#### **6.3. BASELINE PERIOD**

The Baseline Period begins at randomization and ends at the start of the Observation Period. The following information will be recorded as close to the start of the Observation Period as possible. Data from standard of care tests may be used as baseline data, as long as it is captured within the time frames noted.

- **Demographic Data**
  - Date of birth
  - Gender
  - Race/ethnicity
- **Hospitalization Data**
  - Hospital Admission Date
  - Hospital Admission Diagnosis
  - ICU Admission Date
  - ICU Admission Diagnosis
- **Vital Signs/Physical Assessment**
  - Temperature
  - Blood Pressure, heart rate, body weight
  - EKG (**within 12 hours prior to the start of Observation Period**)
  - Sequential Organ Failure Assessment (SOFA Score)

- Physical Exam
  - Urine Output (previous 24 hours)
- **Clinical Laboratory Tests (within 12 hours prior to the start of Observation Period)**
  - CBC with differential
  - BUN/Creatinine
  - Na, K, Cl, HCO3, Ca, Mg, Ionized Ca, PO4
  - ALT, AST, LDH, Bilirubin, ALP, Total Protein, Albumin, Glucose
  - PT, PTT, INR
  - Haptoglobin
  - Urinalysis (if urine available)
- **Respiratory**
  - Status – Ventilator support (yes/no; date of intubation)
  - If on Vent: Mode, NO, FiO2, Settings (TV, PEEP, RR)
  - If on Vent with an arterial line: Arterial Blood Gas (12 hours prior to start of Observation Period)
  - If on Vent without an arterial line: Arterial Blood Gas (24 hours prior to start of Observation Period)
  - If not Vented: Supplemental oxygen requirements
- **Blood for Research**
  - Blood sample will be sent to an outside laboratory for testing of biomarkers such as IL6, IL10, Elastase, and GCSF.
- **Other (Event-driven)**
  - All the medications and blood products administered to the patient in the 24 hours prior to start of Observation Period.
  - Adverse Events occurring since randomization, unless directly related to screening procedure
  - Diagnostic/Therapeutic Procedures in the 24 hours prior to start of Observation Period.
  - Microbiology/culture data

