## 12.2. DETERMINATION OF SAMPLE SIZE

The efficacy null and alternative hypotheses to be assessed are as follows:

$$H_0: \lambda_{C+S} = \lambda_C$$

vs.

$$H_1: \lambda_{C+S} \neq \lambda_C$$

where  $\lambda_{C+S}$  and  $\lambda_C$  are the true 60 day mortality hazard rates for the CRRT+SCD and CRRT alone groups, respectively. The null hypothesis will be tested at the overall two-sided 0.05 level of significance at 80% power. Under the assumptions:

1.  $\lambda_C = 0.01155$  when time to mortality is measured in days (leading to a 50.0% mortality rate at 60 days for CRRT alone);  $\lambda_{C+S} = 0.00718$  when time to mortality is measured in days (leading to a 35.0% mortality rate at 60 days for CRRT + SCD);
2. As described in the SCD-003 Protocol, CytoPherx has assumed a mortality rate of 50% for control and 35% for SCD.

For the control mortality estimate, a 2004 publication [20] was used which summarized mortality data for subjects with acute renal failure (ARF) requiring renal replacement therapy (RRT) in the intensive care unit. A table from this publication is reproduced below (Table 9). In this table, the mortality of subjects who received CRRT (“Dialysis”) is compared to those who did not (“% Mortality No Dialysis”). A weighted average was calculated by weighting the observed value for “% Mortality Dialysis” by the number of subjects enrolled. We found that the weighted mortality of subjects who received CRRT was 58.3%, based on this literature analysis of 5,810 subjects.

| Variable          | Ref. | Year | N    | Location                    | % Mortality No Dialysis | % Mortality Dialysis |
|-------------------|------|------|------|-----------------------------|-------------------------|----------------------|
| Brivet et al      | [26] | 1996 | 360  | Multicenter, France         | 43%                     | 64%                  |
| Liano et al       | [5]  | 1998 | 748  | Multicenter, Spain          | 53%                     | 79%                  |
| De Mendonca et al | [27] | 2000 | 1411 | 16 countries, Europe        | NA                      | 44%                  |
| Silvester et al   | [28] | 2001 | 299  | Multicenter, Australia      | NA                      | 47%                  |
| Metniz et al      | [7]  | 2002 | 839  | Multicenter, Austria        | 39%                     | 63%                  |
| Clermont et al    | [29] | 2002 | 254  | Pittsburgh, USA             | 23%                     | 57%                  |

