| Guerin et al      | [30] | 2002 | 587  | Multicenter, France         | NA                      | 71%                  |
| Metcalfe et al    | [31] | 2002 | 89   | Multicenter, Scotland       | NA                      | 74%                  |
| Mehta et al       | [32] | 2002 | 605  | Multicenter, California USA | 39%                     | 61%                  |
| PICARD            | [20] | 2003 | 618  | Multicenter, USA            | 24%                     | 45%                  |

Table 9 Several recent studies of ARF in the ICU

In our proposed pivotal study, the assumed 60-day mortality rate for subjects receiving CRRT only (control subjects) is 50%. This is a conservative estimate

since, based on the literature, the actual control mortality rate might be expected to be slightly higher.

The observed 60 day mortality rate for SCD therapy was 29.2% in the Pilot study with data available for 24 subjects. For the pivotal study, we have increased the assumed mortality rate to 35% to allow for variability in response across a broader population of subjects and treatment centers;

3. The statistical test to compare treatments is the log-rank test;
4. The study will be carried out using an adaptive design approach; specifically, there will be one formal interim analysis on mortality using the log-rank test after 50% of the subjects achieve 60 day follow-up (or would have achieved 60 day follow-up had they not died or prematurely withdrawn from the study ); treatments will be compared via the log-rank test at this interim analysis using the O'Brien-Fleming two-sided significance levels (0.00305) for the interim analysis (leaving a two-sided significance level of 0.049 for the final analysis); only subjects achieving 60 day follow-up (or who would have achieved 60-day follow-up had they not died or prematurely withdrawn) will be used in the interim analysis; note that if significance is shown in the interim analysis, a decision to stop the trial will only be made after consultation with the FDA; if significance is not shown at this interim analysis, then the DSMB will be provided with sample size re-calculations required to maintain at least 80% power for a statistically significant CRRT+SCD effect by the end of the study, conditioned on the interim results (details are provided below).

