#### 12.5. PRIMARY ENDPOINT

The primary endpoint in this trial is time to mortality through 60 days post-randomization. The Kaplan-Meier curve of time (days) to mortality through 60 days post-randomization will be presented, as will the Kaplan-Meier estimate of the 60 day mortality rate. In addition, the raw number and percentage of subjects who died by 60 days will be presented by treatment group. Treatment groups will be compared on time to mortality through 60 days using the log-rank test. The analysis will be carried out for the ITT (primary) and Per-Protocol (secondary) analysis set. It is anticipated there will be few randomized subjects who prematurely withdraw from the trial. Subjects who do not die will be censored at 60 days or at the last known time alive, whichever is earlier.

Due to one formal interim efficacy analysis following which the DSMB may recommend an increase in sample size (based on the observed treatment difference seen at the interim analysis) beyond the initially planned 172 randomized patients (see Section 12.8 for details), the final analysis comparing treatments on the primary endpoint does not use the conventional log-rank test p-value to determine if a statistically significant treatment difference exists. Instead it uses a weighted test statistic,  $T^*$ , proposed by Cui, Hung and Wang [33] in which the independent test statistics of the two stages (interim and final) are combined by pre-specified weights,  $w_1$  and  $w_2 = 1 - w_1$ , where  $w_1$  is the proportion of the total *initially* planned number of patients at which the interim analysis is performed. In the present case the trial is designed for 172 randomized subjects per group with an interim analysis after 50% of the patients achieve 60 day follow-up (or would have achieved 60 day follow-up had they not died or prematurely withdrawn). Thus, the planned information time proportions are  $w_1 = 50\%$  for first stage and  $w_2 = 1 - w_1 = 50\%$  for the second stage.

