## **12.9. EXPLORATORY ANALYSIS**

In addition a number of exploratory analyses will be conducted. No formal statistical hypothesis tests will be conducted. Predictors of survival will be assessed using Cox proportional hazards regression utilizing univariate and multivariate models to assess association of selected parameters with the primary outcome. Some parameters to be assessed may include gender, age, race/ethnicity, presence of co-morbidities, type of CRRT modality, SOFA score and RIFLE predicted outcomes. Additional regression models may include interaction terms for the selected parameters to assess for evidence of a differential treatment effect. Other exploratory analyses on additional outcome measures will describe the following outcomes in the two randomized groups: infection as defined in Appendix D, pressor free days, recovery of renal function, SCD integrity, ICU LOS, Hospital LOS, duration of Renal Support, CRRT circuit life analysis and fluid removal analysis. Continuous outcomes will be summarized with sample size, mean, median, standard deviation, minimum, maximum and 95% confidence intervals; categorical outcomes will be presented with the counts and percents of subjects in each category along with 95% confidence limits. Additional, non pre-specified exploratory analyses may also be conducted.

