### Interpretation:

1. Minimum total score: 0
2. Maximum total score: 24
3. The higher the organ scores the greater the organ dysfunction.
4. The higher the total scores the greater the multi-organ dysfunction.

|                     | MORTALITY RATE BY MODIFIED SOFA SCORE |          |          |          |          |
|---------------------|----------------------------------------------|----------|----------|----------|----------|
| ORGAN SYSTEM | 0                                     | 1 | 2 | 3 | 4 |
| Respiratory         | 20%                                          | 27%      | 32%      | 46%      | 64%      |
| Cardiovascular      | 22%                                          | 32%      | 55%      | 55%      | 55%      |
| Coagulation         | 35%                                          | 35%      | 35%      | 64%      | 64%      |
| CNS                 | 26%                                          | 35%      | 46%      | 56%      | 70%      |
| Liver               | 32%                                          | 34%      | 50%      | 53%      | 56%      |
| Renal               | 25%                                          | 40%      | 46%      | 56%      | 64%      |

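### The unadjusted primary log-rank test is valid and correctly sized, but it leaves unused the efficiency that baseline SOFA and age, both already collected, could supply

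*Protocol*

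**What the plan says.** Section 12.5 states the primary comparison: "Treatment groups will be compared on time to mortality through 60 days using the log-rank test". The sample-size section (12.2) names the same test. Section 12.5 then builds the stage-one statistic Z(1), the end-of-study statistic Z* and the weighted statistic T* from two log-rank tests, and declares this the primary analysis. No covariate or stratum is named. The one covariate list that 12.5 defers to the SAP belongs to the imputation model of a sensitivity analysis.

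The design inputs in 12.2 are: "The null hypothesis will be tested at the overall two-sided 0.05 level of significance at 80% power"; control "leading to a 50.0% mortality rate at 60 days for CRRT alone"; treatment "leading to a 35.0% mortality rate at 60 days for CRRT + SCD"; and, after the interim look at 0.00305, "leaving a two-sided significance level of 0.049 for the final analysis". The required size is 166 evaluable per group, with 172 randomized.

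On the covariates:

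- Section 6.3 lists SOFA and date of birth among the baseline data.
- Appendix A tabulates mortality by organ score (respiratory 20% to 64%, CNS 26% to 70%, renal 25% to 64% from score 0 to 4) and adds: "The higher the total scores the greater the multi-organ dysfunction".
- The China study (2.3.4.1) matched its historical controls on age and SOFA when comparing mortality.
- In the pivotal trial, section 12.9 offers both only as candidates, with no formal testing: "Some parameters to be assessed may include gender, age, race/ethnicity, presence of co-morbidities, type of CRRT modality, SOFA score and RIFLE predicted outcomes".
- Randomization (6.2) is stratified by center and severe sepsis, not by SOFA or age.

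**The concern.** A covariate that predicts death and is measured before treatment explains variation that an unadjusted test leaves in the comparison. If SOFA and age are prognostic here, an adjusted treatment statistic has more power at the same sample size. With power planned at 80%, and an adaptive rule under which the DSMB may recommend up to doubling enrolment, a few points have practical value.

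There is also a question of credibility. With a SOFA standard deviation of about 3.3 and 166 per group, the difference in mean baseline SOFA has a standard error of 3.3 × √(2/166) = 0.36 point. If chance leaves the arms visibly unequal, the primary result has no pre-specified severity-adjusted counterpart in the protocol. An adjusted model chosen afterwards would be open to the charge of selection.

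**Working it through.** **1. Reproduce the plan's figure.** Hazards 0.01155 and 0.00718 per day give 60-day mortality of 1 − exp(−60 × 0.01155) = 50.0% and 1 − exp(−60 × 0.00718) = 35.0%. The hazard ratio is 0.00718/0.01155 = 0.6216, with log −0.4754. Mean mortality is 0.425.

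Schoenfeld events = 4(z for alpha/2 + z for power)² / (log HR)².

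- At 0.05: 4 × (1.960 + 0.842)² / 0.226 = 139 events; 139/(2 × 0.425) = 164 per group.
- At 0.049: 140 events, 165 per group.
- Power at 166 per group and 0.049: 332 × 0.425 = 141.1 events, 80.4%.

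The stated 166 is therefore right for an unadjusted log-rank test.

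**2. Choose covariate effects.** These are assumptions, because the protocol gives no hazard ratio for total SOFA or for age. Spreads come from Table 5: SOFA SD 3.64 and 3.05, taken as 3.3; age SD 13.85 and 17.15, taken as 15.5 years. The combined log-hazard SD is √[(3.3 × log HR per SOFA point)² + (1.55 × log HR per decade)²]. For HRs of 1.10 and 1.20 this is √(0.315² + 0.283²) = 0.42.

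Appendix A gives only a rough guide. On the complementary log-log scale, its single-organ gradients from score 0 to 4 run from 0.19 (liver) to 0.38 (respiratory) per organ point. They do not give a total-score slope. An assumed 0.10 to 0.20 per total point, with SDs of 3.0 to 3.64, gives a log-hazard SD of 0.30 to 0.73 from SOFA alone.

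**3. Simulate.** The set-up was 166 per group, exponential survival, marginal 60-day mortality held at 50% and 35%, and looks at 0.00305 and 0.049. The unadjusted log-rank was compared with the treatment Wald test from a Cox model containing both covariates. With no sample-size increase, t1/t* = 0.5 and w1 = w2 = 0.5, so T* = √0.5·Z(1) + √0.5·(√2·Z* − Z(1)) = Z*.

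| HR per SOFA point / per decade | Log-hazard SD | Unadjusted | Adjusted | Gain (points) |
|---|---|---|---|---|
| 1.00 / 1.00 | 0 | 80.4% | 80.1% | −0.3 |
| 1.05 / 1.10 | 0.22 | 81.0% | 81.2% | 0.2 |
| 1.10 / 1.20 | 0.42 | 80.2% | 83.2% | 3.0 |
| 1.15 / 1.30 | 0.61 | 81.1% | 87.4% | 6.3 |
| 1.20 / 1.40 | 0.80 | 81.4% | 90.8% | 9.4 |

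The first row used 3,000 trials and the others 10,000, so the simulation standard error of a power is about √(0.8 × 0.2/10,000) = 0.4 point for the latter. Type I error under the 1.10/1.20 scenario was 4.9% unadjusted and 5.0% adjusted.

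A separate simulation with one prognostic score and no interim look gave, unadjusted and adjusted, 80% and 81% at SD 0.30, 79% and 83% at 0.45, 81% and 86% at 0.60, and 81% and 90% at 0.75.

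**4. Express it in patients.** Adjusted power of about 80% needed about 150 per group (1.10/1.20), 135 to 142 (1.15/1.30) and 120 (1.20/1.40), against 166. For the two moderate cases that is 1 − 150/166 = 10% to 1 − 135/166 = 19% fewer.

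**The case against.** The strongest reply is that nothing in the plan is wrong. The log-rank test is named consistently, the sample size was computed for it, and the planned power is met. A reader might infer that the trial is underpowered or that 166 is an error; step 1 of the working shows neither. This objection stands in full and sets the status of the point: an efficiency improvement.

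The size of the gain is assumed. The SOFA spread comes from two groups of nine. Appendix A is uneven: cardiovascular mortality is flat at 55% over scores 2 to 4, and coagulation is flat at 35% over 0 to 2. All patients here have ATN on CRRT, which narrows the renal score. The China regression (2.3.6) found neither age nor SOFA significant, although nine against nine is little evidence either way. Support for age is weaker than for SOFA, resting on matching and an exploratory list. So a gain of 5 points or more cannot be claimed; it needs a log-hazard SD near 0.6.

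A reader might also infer that the planned estimates are biased towards the null. The protocol's estimates are Kaplan-Meier mortality rates and their difference, which are marginal quantities and are not attenuated. A conditional hazard ratio differs from a marginal one; that is not bias. Nor does chance imbalance invalidate the test, because its type I error already allows for it.

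Finally, it is tempting to say that SOFA is recorded for every patient. The Baseline Period starts at randomization (6.3), and the ITT set is all randomized subjects (12.3). Someone who dies or withdraws before therapy starts could lack a score.

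Two answers remain. The data collection is already planned, and in the simulation adjusting for useless covariates cost about 0.3 point, within simulation error. An SAP, which was not available, may add a supportive adjusted analysis, but the protocol itself fixes the primary statistic.

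**Conclusion.** The point holds as lost efficiency in a valid and correctly sized analysis. Adjusting for baseline SOFA and age would add roughly 0 to 10 power points at 166 per group for log-hazard SDs of about 0.30 to 0.75, and about 3 to 6 points for moderate effects. Almost nothing is lost if they are not prognostic. The direction is secure if SOFA predicts death in this population, as Appendix A suggests; the magnitude rests on assumed slopes and on a spread taken from very small groups. The simulations did not model a sample-size increase, so the figures apply to the trial at its initial size. The documents do not support a claim of insufficient power, biased mortality estimates or complete SOFA data.

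**What to change.** Before any unblinded look, amend 12.5 so that Z(1) and Z* are the treatment statistics from a Cox model with treatment, baseline total SOFA and age as continuous covariates. A log-rank test stratified by pre-set baseline SOFA category is an acceptable alternative. Use the identical statistic at both stages of T*.

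State a simple rule, blind to treatment arm, for missing baseline SOFA, such as the pooled baseline mean, so that every randomized patient stays in the ITT analysis. Re-run the type I error simulations for T* with the new statistic, including the sample-size increase. Keep the plain log-rank test, the Kaplan-Meier curves and the 60-day mortality difference as the supportive marginal analysis.

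No new data item is needed, but the cost is more than wording. The adjusted hazard ratio is conditional on SOFA and age. It is therefore not the marginal effect used in the re-estimation formula of 12.8, which compares 60-day mortality differences, and the text should say so. The missing-data rule must be written and the simulations repeated.

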### **6.2. RANDOMIZATION**

A centralized randomization system has been established with 24-hour availability to provide a mechanism to randomize subjects and enroll them in the study. Once the patient meets all eligibility criteria, **including being on CRRT**

**for a minimum of 4 hours, but no longer than 24**, and has signed informed consent, the site will enter the patient into the randomization system.

Patients will be randomized in a 1:1 allocation utilizing a random permuted block design into either the control or treatment arm, stratified by study center and the presence of severe sepsis or not. (Appendix C). This should occur as close to the start of the Observation period as possible while also allowing time for baseline tests and data to be completed before the patient has been on CRRT for 24 hours. Patients will then be considered enrolled in the study and given a study number. Randomization results will not be revealed to the clinical team and patient until immediately prior to start of first treatment.

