Hence, two log-rank tests will be performed. The first (interim) log-rank test will be based on all patients who achieved 60-day follow-up (or would have achieved 60 day follow-up had they not died or prematurely withdrawn) at the time of the interim analysis. The log-rank test Z statistic for treatment effect from this model is denoted as  $Z^{(I)}$ . The second log-rank test will be based on all patients in the full analysis set at the end of the study. The log-rank Z statistic for treatment effect from this model is denoted as  $Z^*$ . Then define

$$Z^{(2)} = \frac{1}{\sqrt{1 - \frac{t_1}{t^*}}} Z^* - \frac{\sqrt{\frac{t_1}{t^*}}}{\sqrt{1 - \frac{t_1}{t^*}}} Z^{(1)}$$

where  $t_1$  = ratio of observed number of patients at the interim analysis to the *initially planned* total required number of randomized patients (172); and  $t^*$  = ratio of the number of randomized patients at the end of the trial to the initially planned total number of randomized patients (172).  $Z^{(2)}$  is independent of  $Z^{(1)}$  and captures the information about the treatment effect in  $Z^*$  that is not in  $Z^{(1)}$  [34].

At the final analysis, the test statistic used to compare treatments will be the weighted sum of  $Z^{(1)}$  and  $Z^{(2)}$  as defined above, using the square root of the planned proportions (square roots of  $w_1$  and  $w_2$  where  $w_1 = w_2 = 1 - w_1 = 0.5$ ) as the weights, respectively. Specifically, the weighted test statistic for the final analysis,  $T^*$ , is defined as:

$$T^* = \sqrt{w_1} Z^{(1)} + \sqrt{w_2} Z^{(2)}$$

This combined test statistic  $T^*$  will be used to test the treatment effect with respect to the primary outcome at the final analysis. This test statistic controls the overall type I error in the presence of a sample size increase. This has been confirmed by computer simulations.

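### The primary log-rank statistics leave out severe sepsis, a randomization stratum: some efficiency is forgone if it predicts death, but validity and the stated power hold

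*Protocol*

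**What the plan says.** Protocol section 6.2 allocates patients 1:1 in permuted blocks, "stratified by study center and the presence of severe sepsis or not". Section 12.5 then sets the primary comparison: "Treatment groups will be compared on time to mortality through 60 days using the log-rank test". For the two-stage design it adds "Hence, two log-rank tests will be performed": Z(1) at the interim analysis and Z* at the end, combined into T* with fixed weights. Section 12.2 bases the sample size on the same test ("The statistical test to compare treatments is the log-rank test") and fixes the "two-sided significance levels (0.00305) for the interim analysis (leaving a two-sided significance level of 0.049 for the final analysis".

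No stratum or covariate is named for the test in any of these places. Severe sepsis otherwise enters the efficacy analysis only as a secondary-endpoint subgroup (sections 3.4 and 12.6). For center, section 12.5 allows patients to be pooled across sites in the primary analysis unless a qualitative interaction appears.

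**The concern.** Stratified allocation holds the arms close to balanced within the severe-sepsis groups. If those groups differ in mortality, the numerator of the log-rank statistic varies less from trial to trial than the plain log-rank variance allows. The unstratified test then rejects too rarely under the null. Under the alternative, mixing high-risk and low-risk patients also dilutes the hazard ratio. Both effects cost power on the primary endpoint, and the factor that would recover it is already recorded for every patient.

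**Working it through.** **1. The plan's own figure.** Inputs from section 12.2: control hazard 0.01155 per day ("leading to a 50.0% mortality rate at 60 days for CRRT alone"), treatment hazard 0.00718 per day ("leading to a 35.0% mortality rate at 60 days for CRRT + SCD"), and "The null hypothesis will be tested at the overall two-sided 0.05 level of significance at 80% power".

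- Hazard ratio = 0.00718 / 0.01155 = 0.6216, with log −0.4754.
- Schoenfeld events = 4 × (1.960 + 0.842)² / 0.4754² ≈ 139. Mean event probability is (0.50 + 0.35)/2 = 0.425, so 139 / 0.425 / 2 = 163.5, or 164 per group. At the final level of 0.049, this becomes 140 events and 165 per group.
- Two-look power at 166 per group, with levels 0.00305 and 0.049, is 80.5% by Schoenfeld and 79.0% by Freedman. The overall alpha of the two levels is 0.0500.

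The stated 166 per group therefore reproduces for an ordinary, unstratified log-rank test.

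**2. Unstratified against sepsis-stratified, overall mortality held at the plan's 50% and 35%.** Simulation with 344 patients, 30 centers, blocks of 4 within center-by-sepsis cells, exponential times, and a single two-sided 0.05 test. Block size, 50% severe-sepsis prevalence and the sepsis hazard ratio are assumptions. There were 8,000 replicates under the null and 5,000 for power.

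| Sepsis hazard ratio | Type I, unstratified | Type I, by sepsis | Power, unstratified | Power, by sepsis | Power, by center × sepsis |
|---|---|---|---|---|---|
| 1 | 4.7% | 4.6% | 81.2% | 81.2% | 77.0% |
| 1.5 | 5.1% | 5.2% | 83.0% | 83.6% | 79.8% |
| 2 | 4.4% | 5.2% | 82.7% | 84.2% | 79.9% |
| 3 | 4.1% | 5.2% | 83.4% | 87.1% | 82.9% |

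At 40% and 60% prevalence, the gain from stratifying by sepsis was about 0, 0.5, 1 to 2 and 4 to 5 points. Unstratified type I error in those smaller runs (3,000 replicates) was 3.5 to 3.9% at hazard ratio 2 and 3.0 to 3.7% at 3.

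**3. The two-look rule.** If the sample size is not increased, t1/t* = 0.5 and T* = √0.5·Z(1) + √0.5·(√2·Z* − Z(1)) = Z*. The rule can therefore be simulated directly. Assumptions here: 55% severe sepsis, hazard ratio 0.6216 within each stratum, 344 patients, 6,000 replicates for power and 12,000 for type I error.

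| Control mortality, septic / not | Sepsis hazard ratio | Power, unstratified vs by sepsis | Type I, unstratified vs by sepsis |
|---|---|---|---|
| not prognostic | 1 | 81.0% vs 80.9% | 5.1% vs 5.1% |
| 60% / 38% | 1.9 | 80.8% vs 82.2% | 4.5% vs 5.1% |
| 65% / 32% | 2.7 | 79.0% vs 82.4% | 3.9% vs 5.0% |
| 70% / 26% | 4.0 | 75.1% vs 81.6% | 3.0% vs 4.9% |

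The hazard ratios follow from ln(1 − septic mortality) / ln(1 − other mortality); for example, ln 0.40 / ln 0.62 = 1.92.

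**4. Why some unstratified entries in step 3 fall below 80%.** Holding 0.6216 within strata makes overall treatment-arm mortality higher than the plan's 35.0%. In the last row it is 0.55 × (1 − 0.30^0.6216) + 0.45 × (1 − 0.74^0.6216) = 0.55 × 0.527 + 0.45 × 0.171 ≈ 36.7%. With overall mortality held at 50% and 35% and 332 patients (2,000 replicates, Monte Carlo standard error about 0.9 point), unstratified power is 80.2%, 79.7%, 80.9% and 83.7% at sepsis hazard ratios 1.5, 1.92, 2.72 and 4.0. Stratifying by sepsis adds 0.3, 0.9, 4.0 and 5.1 points.

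**5. Center.** Up to 30 centers give up to 60 cells for 344 patients, or about 5.7 per cell. In step 2, stratifying by every cell loses about 4 points against sepsis alone. With an assumed center effect (SD 0.4 on the log hazard, 60% prevalence), it still trails sepsis alone at every hazard ratio: 81.0% vs 82.2%, 82.2% vs 83.9%, 83.5% vs 85.3% and 85.7% vs 87.0%.

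**The case against.** **The size rests on figures the protocol does not give.** Section 6.2 states no reason for choosing severe sepsis as a stratum. Balancing the arms for the septic secondary endpoint would explain it equally well. The nearest figure, 58% in section 2.1, is sepsis rather than severe sepsis, in two groups of 12. This stands, and it is why the size is given as a range that includes zero.

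**The extreme case fits this population poorly.** Patients without sepsis must have a non-renal organ SOFA score of at least 2. For such scores, the Appendix A table lists mortality of 32 to 70%, so 26% lies below every entry. This also stands: a hazard ratio near 4 is an upper bound.

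**The choice of test may be left to the analysis plan.** The protocol never uses the word unstratified, and a separate analysis plan, not seen here, could add the stratum. But section 12.5 already fixes the statistics, formulas and weights, and section 12.2 fixes the levels. Where section 12.5 does defer, for the imputation covariates, it says so. The point is about a choice that the protocol states, not a missing detail.

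**Stratifying the randomization does not make an unstratified log-rank test wrong.** Correct. The sample-size, interim and final tests agree with one another, and type I error is not inflated.

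**Conclusion.** The written primary test is valid but forgoes efficiency to the extent that severe sepsis predicts death. The power given up against a sepsis-stratified test is:

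- about 0 to 0.5 point at a sepsis hazard ratio of 1 to 1.5;
- about 1 to 2 points at 2;
- about 3 to 5 points near 3;
- 5 to 7 points only near 4.

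Type I error falls to about 4 to 4.5% at hazard ratios of 2 to 3, with some smaller runs lower. These sizes assume 40 to 60% prevalence, exponential survival and blocks of 4. No simulation showed a meaningful loss from stratifying by sepsis.

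A reader might infer that the trial is underpowered or that its significance level is compromised. The protocol supports neither reading. Under its own 50% and 35% mortality, the unstratified test holds about 80% power at the stated sample size, and its error is on the conservative side.

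**What to change.** Before the interim analysis, state in section 12.5 that Z(1) and Z* are log-rank statistics stratified by severe sepsis as recorded at randomization. Keep the same weights and critical values at both stages, and report the matching stratified Cox hazard ratio. Do not stratify the primary test by all center-by-sepsis cells, because that costs power relative to sepsis alone. Use the pooled centers of section 12.5 only as a sensitivity analysis.

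The cost is about one sentence. The stratum is already held in the randomization system, and the planned sample size does not change.
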